***Audits in patients discharged after acute myocardial infarction or coronary artery bypass surgery:***							
USA (39)	201 752	NR	30%	34%	83%	NR	NR
USA (37)	1710	12%	NR	44%	53%	NR	NR
USA (38)	622	37%	NR	23%	46%	25%	15%
USA (45)	190 015	NR	31%	NR	NR	NR	NR
USA (47)	25 000	NR	NR	NR	81%	NR	NR
Europe (40)	3379	58%	43%	66%	84%	21%	41%
Ontario(48)	9667	40%	65%	68%	NR	NR	NR
Quebec(48)	4790	43%	57%	68%	NR	NR	NR
British Columbia(48)	2570	42%	58%	61%	NR	NR	NR
Nova Scotia(48)	761	36%	58%	83%	NR	NR	NR
Alberta (APPROACH patients)**	5104	34%	39%	61%	81%	NR	NR

Note that while the general practice audits represent cross-sectional data at varying times after the diagnosis of CAD, the audits in patients discharged after acute MI generally represent prescribing data between 90 days and 120 days after MI.

* Target cholesterol defined as LDL cholesterol ≤ 2.6 mmol/L or total cholesterol ≤ 5.0 mmol/L.

** Medications in use at the time of the cardiac catheterization (no data available on prescriptions in follow-up). [[name], personal communication, August 2003]

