#### Exclusion criteria

Patients will be excluded if: (1) they have not had a fasting lipid panel done in the six weeks prior to their cardiac catheterization; (2) they are already on a statin at maximal dose; (3) they are on a statin/lipid-lowering drug and the LDL cholesterol level is ≤ 2.5 mmol/l; (4) they are not on a statin but their fasting LDL is ≤ 1.8 mmol/L; (5) they do not have CAD proven on catheterization; (6) they are undergoing catheterization in the setting of an acute coronary syndrome or cardiogenic shock; (7) they die during the catheterization or require emergency bypass surgery; (8) the catheterization is being done as part of a research protocol; (9) they do not have an identifiable primary care physician; (10) they have contraindications to statin use (history of cirrhosis or inflammatory muscle disease, serum creatinine ≥ 200 umol/L, women of child-bearing age, or prior allergy to statins); and/or (11) they are already enrolled in ESP-CAD.

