#### Secondary outcomes

Secondary outcomes will include the provision of other proven efficacious medications for CAD by six months, including ACE inhibitors, beta-blockers, and antiplatelet agents; these medications will be considered independently as individual end-points in eligible patients. Moreover, we will examine changes in the provision of other lipid-lowering medications (fibrates, niacin, and/or resins), as well as self-reported smoking rates, receipt of smoking cessation advice, provision of nicotine replacement products, or buproprion in trial patients within six months of their angiogram. We also will record whether study participants have a fasting lipid profile done in the six months post-angiogram and, for the subgroup of patients who have a fasting lipid profile done during follow-up (i.e., done for clinical reasons by their attending physicians, not mandated by the trial protocol), we will examine the proportion of patients achieving target LDLs compared to baseline. Finally, we also will analyze clinical events (MI, stroke, admissions for CAD, total hospitalizations, and mortality) in the three arms of this study, although the study is not powered to find any differences in these end-points over such a short timeframe.

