### Study procedures and data collection

Baseline data (including demographics, comorbidities, medication use, cholesterol levels, and sociodemographic variables) will be collected by research personnel using a standardized abstraction instrument at the time of the patient's catheterization. The primary source of outcome data for the study will be patient self-report on telephone contact at three and six months, with cross-referencing to pharmacy records for medications, centralized laboratory data for fasting lipid panels, and medical records for clinical outcomes. In an earlier study, we found a high degree of agreement between patient self-report of statin and ACE inhibitor use and data from dispensing pharmacies (simple agreements ranged between 88% to 99% and kappas were 0.78 to 0.93)[83]. Vital status will be queried via the APPROACH database. The outcome data will be abstracted using standardized forms in a secure database housed in the Epidemiology Coordinating and Research (EPICORE) Centre, University of Alberta, Canada.

Investigators, outcome assessors, and study patients will be masked to allocation status. Primary care physicians cannot be blinded to allocation status. Follow-up data will be collected without knowledge of allocation status in an independent and blinded fashion, and statistical analyses will be conducted by a statistician blinded to allocation status.

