#### Other analyses

In examining the secondary outcomes (for example, use of ACE inhibitors, beta-blockers, etc.), we will use similar statistical methods for the primary statin outcome analyses.

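### The LDL-target outcome is set against a baseline LDL that also decided entry, so a before-after reading is distorted; the comparison should be stated as between arms

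*Protocol article*

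**What the plan says.** The Secondary outcomes section restricts this outcome to a subset, "for the subgroup of patients who have a fasting lipid profile done during follow-up", and for them states "we will examine the proportion of patients achieving target LDLs compared to baseline". It gives no target value.

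The Exclusion criteria select on LDL at two levels. Patients are excluded if "they are on a statin/lipid-lowering drug and the LDL cholesterol level is ≤ 2.5 mmol/l", or if "they are not on a statin but their fasting LDL is ≤ 1.8 mmol/L". The qualifying value is recent, because patients are also excluded if "they have not had a fasting lipid panel done in the six weeks prior to their cardiac catheterization".

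Under Study procedures and data collection, "Baseline data (including demographics, comorbidities, medication use, cholesterol levels, and sociodemographic variables) will be collected" at the time of catheterization. No second lipid panel after selection is described, so the value that qualified the patient appears to be the baseline value.

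The only cholesterol target defined anywhere is a footnote to Table 2, which summarises audits from other studies: "Target cholesterol defined as LDL cholesterol ≤ 2.6 mmol/L or total cholesterol ≤ 5.0 mmol/L".

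For secondary outcomes in general, Other analyses says "we will use similar statistical methods for the primary statin outcome analyses". Statistical analyses describes those methods as chi-square comparisons between randomized arms, with logistic regression for variables judged clinically important or differing between arms at p < 0.10.

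**The concern.** When patients are selected because one measurement lies above a line, some re-test below it simply because LDL varies within a person. If the selecting measurement is also the baseline comparator, the proportion below the line rises without any change in treatment.

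The unequal entry cut-offs make the two patient groups behave differently. At a target of 2.5, treated entrants start at 0% by construction. Untreated entrants between 1.8 and 2.5 start at target and cannot newly reach it. The size of any apparent change from baseline therefore depends partly on the mix of treated and untreated patients, not only on care. A rise seen in every arm, including usual care, could be misread as better lipid control. This would remain even if every patient had a follow-up panel.

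**Working it through.** **Inputs from the protocol.** Entry LDL is above 2.5 mmol/L if on a statin or other lipid-lowering drug, and above 1.8 if not on a statin. The planned size is 160 per arm. The protocol states no figure for the LDL outcome, so there is none to reproduce.

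**Inputs assumed.** The protocol gives no LDL mean, SD or within-person correlation. Ranges used:
- Treated patients before selection: mean μ 2.3 to 3.2, SD σ 0.7 to 0.9, correlation ρ between the two measurements 0.6 to 0.9.
- Untreated patients before selection: μ 2.8 to 3.6, σ 0.8 to 1.0.
- Baseline and follow-up LDL bivariate normal, with no change in treatment.

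**Treated entrants, re-test at or below target t.** With a = (2.5 − μ)/σ and b = (t − μ)/σ,

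P(follow-up ≤ t | baseline > 2.5) = [Φ(b) − Φ₂(a, b; ρ)] / [1 − Φ(a)],

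where Φ₂ is the bivariate normal distribution function.

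Example with t = 2.5, μ = 2.6, σ = 0.7, ρ = 0.75: a = b = −0.143, Φ(a) = 0.4432, Φ₂ = 0.3294. The result is (0.4432 − 0.3294)/(1 − 0.4432) = 20.4%, against 0% at baseline.

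Extremes of the grid for t = 2.5:
- μ = 3.2, σ = 0.7, ρ = 0.9: (0.1587 − 0.1155)/0.8413 = 5.1%.
- μ = 2.3, σ = 0.7, ρ = 0.6: (0.6125 − 0.4712)/0.3875 = 36% (36.4% before rounding of the inputs).

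A narrower set of assumptions (μ 2.8 to 3.0, true between-person SD 0.6 to 0.7, within-person SD 0.2 to 0.4) gives 6% to 18%. There ρ = SD²/(SD² + within-person SD²), which runs from 0.69 to 0.92.

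At t = 2.6, treated entrants between 2.5 and 2.6 already count as at target. Over the same grid the baseline proportion is 4% to 14% and the re-test proportion 8% to 43%, so the artefact persists.

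**Untreated entrants already at target on entry.** The proportion is [Φ((t − μ)/σ) − Φ((1.8 − μ)/σ)] / [1 − Φ((1.8 − μ)/σ)].

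Example with t = 2.5, μ = 3.2, σ = 0.8: (0.1908 − 0.0401)/(1 − 0.0401) = 15.7%. Over the grid it is 7% to 28% at 2.5 and 10% to 33% at 2.6. On re-test with no change in care this proportion moves by less than 5 points (largest shift at 2.5: 26.6% to 31.0%).

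**Between-arm comparison under the null.** 20,000 simulated trials used 160 treated entrants per arm, μ = 2.6, σ = 0.8, ρ = 0.75, and the same selection in both arms. A two-sided between-arm test of proportions at 5% rejected in 5.1% of runs. A within-arm McNemar test against baseline rejected in essentially 100%. As a plausibility check, the formula above gives a re-test proportion of 20.75% here, about 33 of 160 patients, all crossing in one direction. The McNemar statistic is then about (33 − 1)²/33 = 31, against a critical value of 3.84.

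**The case against.** The strongest reply is that the article already plans to compare arms. Other analyses carries the primary methods over to secondary outcomes, and those are between-arm tests. The mention of baseline may only describe how target status is expressed; no within-arm test is specified. This largely stands. Randomized arms share the regression to the mean, and the simulated between-arm error rate is nominal. A reader might infer that the trial's LDL comparison between arms is biased by this mechanism; the documents do not support that. The near-certain McNemar rejection concerns a test the protocol does not name and shows only why a before-after reading fails.

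A reader might also infer that the protocol contradicts itself with three LDL targets. It does not: 1.8 and 2.5 are eligibility limits, and 2.6 describes other studies' audits. The target value may properly sit in a fuller document. It follows that 0% at baseline is true of treated patients at 2.5 but not at 2.6, and that untreated patients being at target on entry is true at 2.5 or 2.6 but not at 1.8.

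Finally, this is an opportunistic secondary outcome from clinically ordered panels, with no power claim. That limits its importance. It does not remove the stated baseline comparator, which still has to be reconciled with the analysis sections.

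**Conclusion.** The point holds in a limited form. The protocol names as comparator a value on which patients were selected, at unequal cut-offs, so change from baseline in the proportion at target cannot be read as improved lipid control. With no change in care, roughly 5% to 36% of treated entrants would re-test at or below 2.5, and roughly 7% to 28% of untreated entrants would be there already. Both ranges rest wholly on assumed LDL distributions, on the qualifying panel serving as baseline, and on a 2.5 cut-off that the outcome does not itself state.

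The between-arm contrast is not biased by this mechanism, and the primary statin outcome and its sample size are untouched. Whether selective ordering of follow-up panels biases the contrast is a separate question that this point does not settle. This is a worthwhile clarification of one secondary outcome, not a demonstrated error in the trial's main analysis.

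**What to change.** In Secondary outcomes, replace the comparison with baseline by a between-arm comparison of the proportion at or below one pre-stated analytic LDL cut-off at follow-up, adjusted for baseline LDL and baseline statin use. Add that within-arm change from baseline is descriptive only.

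The adjustment should be fixed in advance. Both covariates are already collected, but as written they would enter the model only if judged clinically important or if they happened to differ between arms at p < 0.10. Both should predict follow-up LDL status, so adjusting for them should sharpen the arm comparison.

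An analysis restricted to patients above the cut-off at baseline is at most an optional sensitivity analysis. It would shrink an already self-selected subset and drop untreated patients with low LDL whom the trial enrols on purpose.

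The cost is one or two sentences, with no new data and no change to sample size.

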### Outcome measures

We decided to focus on only those secondary prevention maneuvers that have strong evidence of survival benefits and are readily measurable from patient self-report and/or examination of pharmacy records. We decided not to examine factors (such as blood pressure control or LDL cholesterol levels) that would require in-person patient assessments, as this would substantially increase the complexity and expense of this study. If the interventions tested in this study are effective, then subsequent studies will extend the interventions (and their assessment) to address other cardiovascular risk factors such as control of blood pressure.

Although we mention five secondary prevention maneuvers in the local opinion leader and unsigned evidence statements (see Additional Files 1 and 2), we chose to emphasize statin prescribing in the statements (and as our primary outcome measure) because we felt the evidence for using statins in all patients with CAD (regardless of baseline cholesterol level) is more robust than the evidence for the use of ACE inhibitors or beta-blockers in all patients. Although the evidence in support of antiplatelet agents also is robust, we chose not to make this the primary outcome because of the likelihood that ASA prescribing may be close to maximal already (see Table 2).

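### The only follow-up LDL analysis the protocol names is the proportion at target; adding a baseline-adjusted comparison of LDL as a continuous measure would use the same data with more power

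*Protocol article*

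**What the plan says.** Under Secondary outcomes, the protocol article restricts the LDL question to patients with a follow-up panel "done for clinical reasons by their attending physicians, not mandated by the trial protocol", and for them "we will examine the proportion of patients achieving target LDLs compared to baseline". Under Other analyses it adds that for secondary outcomes "we will use similar statistical methods for the primary statin outcome analyses". The Statistical analyses section describes those methods as a chi-square test followed by multivariable logistic regression, both for a binary outcome.

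The numeric values exist. A fasting lipid panel in the six weeks before catheterization is a condition of entry (Exclusion criteria), cholesterol is among the recorded baseline data, and follow-up panels are checked against "centralized laboratory data for fasting lipid panels" (Study procedures and data collection).

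No number is attached to the LDL target for this outcome. The nearest definition is the footnote to Table 2, which concerns published audits: "Target cholesterol defined as LDL cholesterol ≤ 2.6 mmol/L or total cholesterol ≤ 5.0 mmol/L".

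**The concern.** Classifying a patient as at target already requires the LDL value, and the cut then discards how far LDL moved. A fall from 4.5 to 3.2 mmol/L counts for nothing if the target is near 2.5. Patients not on a statin may enter with any LDL above 1.8 mmol/L, so some are at such a target before anything is done and cannot newly reach it.

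The primary outcome counts attempted prescribing, even if the drug is later stopped, and the article says the trial is not powered for clinical events. LDL is therefore the only laboratory evidence on whether extra prescribing changed a risk factor. A weak analysis makes a null LDL result more likely when there is a real effect, and such a result could be misread as prescribing having changed while cholesterol did not.

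**Working it through.** **Inputs from the protocol article.** Statin action 20% versus 35%, two-sided 0.05, 80% power, 138 per arm raised to 160 (Sample size). Entry limits: LDL above 2.5 mmol/L if on a lipid-lowering drug, above 1.8 if not on a statin (Exclusion criteria). LDL falls of 25% and 35% (Table 1, the LIPID and 4S rows).

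**Assumptions not in the document.** Baseline LDL normal with mean 3.2 and SD 0.8 mmol/L before truncation at the entry limits; target 2.5; baseline to follow-up correlation 0.6 or 0.8; 20% or 40% already on a statin; 6% fall for a dose increase; 50% to 100% of 160 tested (80, 112 or 160 per arm). Clustering is ignored.

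**1. The plan's own figure.** With pooled p = 0.275, n = [1.960·√(2·0.275·0.725) + 0.842·√(0.20·0.80 + 0.35·0.65)]² / 0.15² = (1.238 + 0.524)² / 0.0225 ≈ 138. It reproduces, and it concerns the primary outcome only. No power is stated for LDL.

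**2. Loss from a cut under a pure normal shift.** Information kept = φ(z_p)² / [p(1−p)], where p is the proportion at target.

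| At target | 10% | 20% | 30% | 50% |
|---|---|---|---|---|
| Information kept | 34% | 49% | 58% | 64% |

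Take a shift that gives the unadjusted mean 80% power at 160 per arm: d = (1.960 + 0.842)·√(2/160) = 0.313 SD. The at-target test then has 53% to 60% power (20% to 50% at target). This is the simple textbook case. The trial's effect is a mixture, because only some patients change treatment.

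**3. Who can cross the line.** Ignoring noise, a 25% fall reaches 2.5 only from a baseline of at most 2.5/0.75 = 3.33 mmol/L, and a 35% fall only from at most 2.5/0.65 = 3.85. Changers who start above those values, or already at or below 2.5, add nothing to the proportion newly at target.

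**4. Simulation of the mixture** (1,500 replicates per case, Monte Carlo error about 1 point). It compares an unadjusted two-proportion test at 2.5 with a linear model on log LDL adjusted for baseline. In these three cases 20% are already on a statin:

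| Tested per arm | LDL fall | Correlation | At target | Adjusted continuous | Repeat run |
|---|---|---|---|---|---|
| 160 | 25% | 0.8 | 18% | 40% | 19% v 39% |
| 112 | 35% | 0.8 | 25% | 40% | 24% v 41% |
| 80 | 25% | 0.6 | 11% | 17% | 11% v 15% |

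Over 24 scenarios the gain was 4 to 22 points, so about 4 to 20 allowing for simulation error.

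**5. Where the gain comes from.** At 160 per arm, removing the cut with no adjustment moved power from 16% to 21%, 19% to 25% and 34% to 37% in three cases, a gain of 3 to 6 points. Against an at-target analysis that is itself adjusted for baseline, the adjusted continuous analysis gained about 3 to 18 points. The benefit needs the continuous scale and the adjustment together.

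**6. Sensitivity to the LDL model.** A second set of assumptions (mean 3.0 or 3.2, SD 0.7 or 0.8, added noise SD 0.4, every statin action giving the full 25% or 35% fall) gave:

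| Tested per arm | At target | Unadjusted mean | Adjusted mean |
|---|---|---|---|
| 80 | 12–28% | 14–27% | 29–41% |
| 160 | 18–50% | 25–50% | 50–67% |

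The gains are larger here because no patient has merely a dose increase with a small fall. The pattern is the same: little from dropping the cut alone, and power below 70% even with adjustment.

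**7. Sensitivity to persistence.** The background cites one-year statin persistence of 43% to 75%. If 60% of actions take effect (an assumption within that range), power is 10–16% at target versus 13–27% adjusted continuous at 160 per arm, and 7–11% versus 9–16% at 80. The ends of these ranges differ by 9 − 7 = 2 up to 27 − 16 = 11 points.

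**The case against.** **LDL is deliberately not a focus.** The article says: "We decided not to examine factors (such as blood pressure control or LDL cholesterol levels) that would require in-person patient assessments". It also limits its interest to attempted practice change and claims no power for LDL. This stands as a reason to rank the point low. The reason given, in-person visits, does not apply to laboratory values that are retrieved anyway.

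**Percent at target is a sensible measure here.** The case for the trial rests on patients not reaching recommended levels, and Table 2 reports that proportion for the cited audits. This stands. A reader might infer that continuous LDL should replace it as the main analysis. The documents do not support that, since the order of the two is a matter of preference.

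**The article does not exclude other analyses.** A reader might infer that LDL will be analysed only as at target or not. The text shows only that no other analysis is named; a fuller plan may add one.

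**The cut is not the main cause of the low power.** A reader might infer that dichotomising alone makes a null result much more likely. Steps 5 and 7 do not bear this out: most of the gain needs baseline adjustment, and a null result is the likelier outcome under either method in nearly all the cases examined. The planned logistic regression could adjust for baseline LDL, but it selects covariates by clinical importance (age and gender are its examples) or by p < 0.10 between arms, so that adjustment is not assured.

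**The tested subgroup is selected after randomization.** The fax may itself prompt testing. A reader might infer that a continuous analysis makes the LDL result trustworthy. It does not: a more precise estimate in that subgroup can still be biased.

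**Conclusion.** The point holds as a minor improvement. The protocol names one analysis of follow-up LDL, on a binary scale, when the values for a more efficient analysis are available. Under the main set of assumptions, a baseline-adjusted continuous comparison has about 4 to 20 points more power than the unadjusted at-target comparison. The gain is larger if every statin action gives a full LDL fall, and roughly 2 to 11 points if 60% of actions take effect. These sizes rest on LDL means, SDs, correlations, a target value and testing fractions that the document does not give. The direction does not change across the ranges tried, and power stays low throughout. No stated figure is wrong, and the primary outcome, the 138 per arm and the 160 per arm are untouched.

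**What to change.** In Secondary outcomes, keep the at-target proportion and add beside it a between-arm comparison of follow-up LDL, or of log LDL read as a percent difference. Use linear regression on arm with baseline LDL and baseline statin use as covariates, and account for clustering by practice. In Other analyses, except this comparison from the sentence that carries over the primary outcome's methods.

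State that both LDL analyses apply only to the clinically tested subgroup, and show the proportion tested in each arm beside them.

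The cost is a sentence or two of wording and one extra regression, with no new data collection. The downside is one more secondary analysis, and a mean LDL difference is less direct than percent at target as a measure of quality of care, which is why both should be shown.
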